#### Questionnaires:

*Demographic/History-* Socio-demographics, symptoms history and modifying factors will be self-reported.

*Pain rating and diagram-* A numeric scale from 0 (no pain) to 10 (worst imaginable pain) will assess current, best, worst intensity in the last 24 hours. A diagram will assess location of symptoms.

*Scoliosis-Research-Society questionnaire (SRS-22r)-* The SRS-22r assesses quality-of-life within 5 domains: function, pain, self-image, mental health (5 questions each), and satisfaction (2 questions).

*3D Physical activity recall (3DPAR)*- quantifies habitual physical activity chosen among 55 activities listed, and their intensities for blocks of 30-min over 3 days. The 3DPAR score is determined using the metabolic equivalent (MET) levels.

*Spinal Appearance Questionnaire*- includes 21 items pertaining to the severity of the deformity within 9 domains (Trunk shift, Waist, Kyphosis, Prominence, Chest, Shoulders, General and Curve) .

*Self-efficacy* – measures self-efficacy for overcoming barriers to physical activity using 8 items rated from 1 (Disagree a lot) to 5 (Agree a lot).

*Global Rating of Change (GRC)*- A 15-point GRC ranging from –7 (very great deal worse) to +7 (very great deal better) will be used.

Physical Exam(Appendix E): An physiotherapist blind to groupings will assess curve type and hip range-of-motion in flexion, extension, internal rotation, the straight-leg-raise and FABERE tests. Sorensen's test will assess back extensor muscle endurance. Lumbar (inclinometers at L5/S1 and T12/L1) and thoracic (C7/T1 and T12/L1) spinal range-of-motion will be recorded: lumbar flexion, extension and side flexions. Scoliometer will record asymmetry during the Adam bending test.

Radiographs- Standing postero-anterior radiographs in a positioning frame at baseline, 6 and 12 months and from every scoliosis clinic visits until discharge will be used to measure the Cobb angle, rotations, apex translation. An experienced evaluator blind to group assignment will extract measures.

Surface topography(ST) – An experienced evaluator will operate four scanners and use a positioning frame to scan torso shape. The following ST parameters will be extracted by digitizing 15 points on de-identified scans (blinding): cosmetic score, shoulder angle, scapula angle, waist asymmetry, trunk rotation, kyphotic and lumbar indices.

## **Analyses:**

Intention to treat (by carrying forward last known value) linear mixedmodel analyses will be used to assess differences in group changes from baseline, to 3 and 6-month while adjusting for covariates. Separate analyses will be conducted for each outcome. To screen for variables associated with each of the outcomes variables, we will use univariate linear mixed models and include all relevant covariates (age, time since menarche, apex levels, physical activity, self-efficacy, and bracing compliance may have associations with risk of progression). Multiple linear mixed models will be tested including covariables found significant at  $P=0.20$  in the univariate analysis, and after screening for multicollinearity. Results will be presented as effect sizes with confidence intervals and one-sided P-values. Statistical analyses will be performed using SAS version 9.1.

For subjects initially in the control group later completing 6 months of exercises, intention to treat linear mixed-model analyses will be used to assess differences between the two periods (standard care vs standard care + Schroth) in changes from baseline, to 3 and 6-month, while adjusting for covariates. Screening for covariates will be done as described above. In this model, treatment period is a dependent factor.

To determine if exercises effects are maintained at 12 months and discharge exams, linear mixed- model analyses will also be used to quantify the effect sizes corresponding to changes from 6 to 12 months and to discharge by combining data from all patients after participating in the exercise program.

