## 5.0 Justification for sample size:

Primary and secondary aim 1: A sample of 129 subjects per group will be sufficient to detect a 0.31 effect size when comparing the change in outcomes between the exercise and control groups with 80% power using a unilateral test and an alpha of 0.05 (104 Schroth and 104 controls in this study + 25 Schroth and 25 controls in the pilot allows a total of 129 per group). We anticipate >80% completion rate based on published data and because the pilot dropout rate was <10%. Our per-protocol sample may drop slightly however, we are planning intent to treat analyses where we will carry-forward the last known observation from our participants.

A unilateral hypothesis is justified, for this superiority trial, by positive published data and our pilot data. The pilot effect size for the Cobb angle was 0.32 and many secondary outcomes had effect sizes exceeding what we are powered to detect as significant. A trial conclusive in favour of exercises would have a significant impact in America. A trial failing to demonstrate positive results would have less impact as Schroth exercises are not currently prescribed. We believe that a 0.32 effect size is clinically important, feasible, and would justify implementing a Schroth program. The trial duration is relatively short which justifies aiming to detect a small effect size (0.2-0.5) .

It would be inadequate to power the trial to detect too small an effect size as patients and families will likely demand evidence of clinically important effects before committing efforts and time required of Schroth exercise programs. For the secondary aim comparing the results of subjects in the control group who first complete 6 months as controls to their results after completing 6 months of Schroth exercises, an effect size of 0.27 (n=106) could be detected as significant with a power of 0.80, an alpha of 0.05 with a unilateral test.

ID: Pro00043397

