## 5.1 Data Collection

- 1.0 **\* Will the researcher or study team be able to identify any of the participants at any stage of the study?**  
☒ Yes ☐ No
- 2.0 **Primary/raw data collected will be** *(check all that apply):*  
**Indirectly identifying information** - the information can reasonably be expected to identify an individual through a combination of indirect identifiers (eg date of birth, place of residence, photo or unique personal characteristics, etc)
- 3.0 **If this study involves secondary use of data, list all original sources:**  
Data from the Specialized Scoliosis database at each site will be extracted as described in the informed consent procedures with the permission of the patient: radiograph measures at baseline, 3, 6, 12 months follow-up, SRS-22 questionnaires at the same times.
- 4.0 **In research where total anonymity and confidentiality is sought but cannot be guaranteed** *(eg. where participants talk in a group)* **how will confidentiality be achieved?**  
Total anonymity is not sought per se. Participants will exercise in groups and get to meet other participants. Participants will be informed of the need to maintain confidentiality of personal information learned in the study. They will also be asked to refrain from informing the evaluator of their study group or of that of other participants.

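### Carrying the last value forward scores a missing 6-month Cobb angle as no change in patients at risk of progression, and it cannot stand in for an attrition allowance

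*Protocol*

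**What the plan says.** Protocol section 2.1, Analyses, defines the primary approach as "Intention to treat (by carrying forward last known value", feeding linear mixed models of change from baseline. Section 4.2, item 5.0, repeats it: "we are planning intent to treat analyses where we will carry-forward the last known observation from our participants".

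That item gives the sample size as "A sample of 129 subjects per group will be sufficient to detect a 0.31 effect size when comparing the change in outcomes", "with 80% power using a unilateral test and an alpha of 0.05", made up of "104 Schroth and 104 controls in this study + 25 Schroth and 25 controls in the pilot". On attrition it says "We anticipate >80% completion rate based on published data and because the pilot dropout rate was <10" per cent. It concedes that the per-protocol sample may fall slightly, and answers this only with carry-forward. It makes no upward adjustment.

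On the timing of the Cobb measurement:

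- Section 2.1, Radiographs: "Standing postero-anterior radiographs in a positioning frame at baseline, 6 and 12 months", then at clinic visits until discharge. The lay summary gives the same times.
- Section 2.1, Procedures: outcomes in general are measured at baseline, 3 and 6 months, but the primary radiographic outcome is named as baseline and 6 months.
- Section 2.1, item 3.0: clinics run every 6 months, and the 3-month assessment is outside routine visits.
- Section 5.1, item 3.0, alone: "radiograph measures at baseline, 3, 6, 12 months follow-up".

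Section 4.2, item 2.0, limits age, and item 3.0 limits Risser sign, so that participants are skeletally immature and can still progress.

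**The concern.** With no film between baseline and 6 months, the last known Cobb value of a patient who lacks the 6-month film is the baseline value. The rule therefore records no progression. In this population that is a favourable result, not a neutral one. The invented values then enter the mixed model as if they had been observed, although such a model can use incomplete records without them.

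Two things are at stake. First, the primary comparison can be biased. The exercise arm carries individual sessions, weekly classes and a daily home programme, so unequal loss is plausible. The test is one-sided in favour of exercise, so an error in that direction is the one that produces a false claim. Second, the sample-size section treats carry-forward as if it preserved the planned power. It fills rows in the data set but adds no information about the treatment effect.

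**Working it through.** **Inputs.** From section 4.2, item 5.0: standardised effect 0.31, 129 per group, one-sided alpha 0.05, power 80%, completion above 80%, pilot dropout below 10%. The documents give no SD, no 6-month progression and no dropout by arm, so values for these below are assumptions. All 129 per group, pilot included, are taken as analysable unless stated.

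**1. The plan's own figure.** n per group = 2(1.645 + 0.842)²/0.31² = 128.7, so 129. Power at 129 = Φ(0.31·√(129/2) − 1.645) = Φ(2.490 − 1.645) = 80.1%. The stated figure reproduces, with zero attrition. Inflating 129 by 1/(1 − m) would have given 144 per group at 10% missing and 162 at 20%.

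**2. Equal loss, carried-forward zeros.** Let a share m of each arm be missing and set to zero change, and let the others have SD 1. The mean difference becomes 0.31(1 − m). The SD becomes about √(1 − m), so the standardised effect is 0.31√(1 − m).

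| Missing m | Estimate (SD) | Standardised effect | Power at 129 per group |
|---|---|---|---|
| 0% | 0.310 | 0.310 | 80.1% |
| 5% | 0.295 | 0.302 | 78.3% |
| 10% | 0.279 | 0.294 | 76.3% |
| 20% | 0.248 | 0.277 | 72.0% |

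The SD formula ignores a small term that depends on the arm means. With it, the 20% row is about 71% to 72%.

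**3. Observed data only.** At 80% completion, 0.8 × 129 ≈ 103 per group. Power = Φ(0.31·√(103/2) − 1.645) = Φ(2.225 − 1.645) = 72%. The effect detectable with 80% power is 2.487/√(103/2) ≈ 0.35. At 90% completion, 116 per group, power is 76%. These match step 2, so carry-forward recovers none of the lost power.

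**4. Unequal loss, no true effect (assumed inputs).** Both arms progress by δ SD. Missing shares are f_S in the exercise arm and f_C in controls. The spurious benefit is (f_S − f_C)δ. Each arm's variance is (1 − f) + f(1 − f)δ², and the standard error is the square root of the summed variances divided by 129.

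| f_S vs f_C | δ | Spurious benefit (SD) | Standard error | z shift | One-sided error |
|---|---|---|---|---|---|
| 20% vs 10% | 0.25 | 0.025 | 0.115 | 0.22 | 7.7% |
| 20% vs 10% | 0.50 | 0.050 | 0.117 | 0.43 | 11.2% |
| 25% vs 10% | 0.25 | 0.0375 | 0.114 | 0.33 | 9.4% |
| 25% vs 10% | 0.50 | 0.075 | 0.115 | 0.65 | 16.0% |

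Average loss is 15% to 17.5%, within the protocol's own expectation. With equal loss and no true effect the error stays at 5%.

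**5. Unequal loss, true effect 0.31.** Controls progress by δ and exercise patients by δ − 0.31. The estimate is 0.31(1 − f_S) + δ(f_S − f_C). In the same four cells it is 0.273, 0.298, 0.270 and 0.307 SD, with rejection rates of 77%, 82%, 77% and 85%. With δ = 0.62 and 20% vs 5% missing, the estimate is 0.34 SD. With the loss reversed (5% exercise, 20% control) it is 0.20 SD, and power is 52%.

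**The case against.** The arithmetic behind 129 is correct for complete data, and several points limit what follows from it.

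- **Direction.** A reader might infer that the imputed zeros always make exercise look better, and that the 80% power fails whatever the pattern of loss. Step 5 shows otherwise. With a true effect of 0.31 and more loss in the exercise arm, the four estimates lie slightly below 0.31, and the rejection rate exceeds 80% when δ is 0.5. That excess comes from bias rather than information, but neither general statement holds.
- **Dropout is not the same as a missing film.** Cobb and SRS-22 values come from routine clinic records, so a patient who stops exercising may still have a 6-month film. The 20% is an upper limit taken from the protocol's completion figure. At 5% missing the power shortfall is under 2 points.
- **Basis of the effect size.** The protocol does not say whether the pilot Cobb effect of 0.32 was computed with carried-forward values. If it was, part of the dilution is already included. Using 0.32, power is 78.6% and 74.3% at 10% and 20% equal loss.
- **A 3-month film.** If the one listed in section 5.1 exists, the carried change need not be zero. It would still be a 3-month change reported as a 6-month one.
- **Enrolment is complete** according to section 4.5, item 2.0, so restating the power cannot enlarge the trial.

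All of these stand, and they limit the size and direction of the problem. None makes carry-forward a sound rule here or a substitute for an attrition allowance.

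**Conclusion.** The rule is wrong as written, because it is fixed in two places and, on the section 2.1 schedule, scores a missing 6-month Cobb angle as no progression. Its effect is conditional. Equal loss shrinks the estimate by the missing share. Unequal loss can bias it in either direction. The one-sided error reaches about 8% to 16% only if there is no true effect, both arms progress (assumed 0.25 to 0.5 SD) and loss is 20% to 25% in the exercise arm against 10% in controls.

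The stated 80% power requires complete data. With equal loss, and if 0.31 is the effect among patients with data, it is overstated by about 2 points at 5% missing, 4 at 10% and 8 at 20%. A reader might conclude that the trial's estimate and power are certainly wrong by a known amount. The documents do not support that, because they give neither the share of missing films by arm nor the basis of the pilot effect.

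**What to change.** 1. Delete carry-forward from section 2.1, Analyses, and section 4.2, item 5.0. Fit the planned linear mixed model to observed data from all randomised patients.
2. State that 6-month clinic radiographs and SRS-22 are extracted for patients who stop exercising, unless consent to data use is withdrawn.
3. Add a sensitivity analysis for data not missing at random, for example multiple imputation based on the control arm.
4. Restate the power at an effect of 0.31: about 72% at 80% completion (103 per group, detectable effect about 0.35) and 76% at 90%. Say whether the pilot 0.32 was computed with carried-forward values.
5. Reconcile the 3-month radiograph in section 5.1 with the schedule in section 2.1.

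The cost is wording, slightly more analysis and a less favourable stated power. No new visits are needed, and the clinic records are already being accessed. The change removes the bias caused by the imputed zeros. It does not recover power, and the mixed model still assumes that data are missing at random, which is why step 3 is needed.

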#### Schroth exercises:

Patients for which the SRS guidelines would recommend observation as standard of care will do exercises alone. Patients for which the SRS guidelines would recommend bracing will do exercises in addition to being prescribed a brace.

*Private sessions-* During the first 2 weeks, patients will attend 5 1-hour-long individual sessions to learn Schroth principles, exercises and correct breathing, and to confirm independent adequate performance with a checklist.

*Home exercises-* A 30-min. daily home exercise program of 3 to 4 exercises will be adjusted during the first 6 months using an algorithm. Compliance will be monitored using a logbook for 6 months. Completion exercises during the last 12 months will also be monitored using a logbook.

*Group Sessions-* Classes increase compliance. Patients will attend weekly 1-hour-long group therapist-led exercise classes. Adequate

exercise performance will be assessed using the checklist. Pain will be monitored.

*Algorithm* – An algorithm guides exercise prescription, intensity and progression from static to dynamic execution. Prescription begins with easier exercise. If performed adequately, a more challenging exercise will be tried. If performance is inadequate, an easier exercise will be attempted. Exercises performed adequately will be prescribed.

At follow-up, if performance is adequate, dosage will increase to target intensity. Target intensity increases repetitions aimed to enhance endurance. Final tension intensity is nearly maximum isometric contraction held in corrected posture.

During the COVID-19 pandemic, the few participants still receiving exercises will be offered the choice to receive therapy in person or via videoconference. Our therapist [name] has access to a secure videoconferencing system (JaneApp) to deliver this therapy remotely. Alternatively [name] has access to a secure ZOOM space. No recording is made during the videoconferencing session.

Controls: Controls will receive the standard of care appropriate for their curves (observation or bracing prescribed as per SRS guidelines), and will complete baseline, 3 and 6 months exams. After 6 months they will cross-over to the treatment group.

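### The sample size makes no allowance for correlation among Schroth patients who share classes, and the analysis section specifies no term for it

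*Protocol*

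**What the plan says.** Under Schroth exercises (section 2.1), the exercise arm receives five individual sessions, a daily home programme and shared classes: "Patients will attend weekly 1-hour-long group therapist-led exercise classes". Section 5.1 (item 4.0) confirms this: "Participants will exercise in groups and get to meet other participants". Controls receive observation or bracing for the first 6 months and join the exercise programme only afterwards.

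The sample size (section 4.2, item 5.0) reads: "A sample of 129 subjects per group will be sufficient to detect a 0.31 effect size when comparing the change in outcomes", "with 80% power using a unilateral test and an alpha of 0.05". The 129 is made up as follows: "104 Schroth and 104 controls in this study + 25 Schroth and 25 controls in the pilot allows a total of 129 per group". The item gives no ICC, class size, number of therapists or design effect, and neither does any other part of the protocol.

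The Analyses part of section 2.1 states: "linear mixedmodel analyses will be used to assess differences in group changes from baseline, to 3 and 6-month while adjusting for covariates". The candidate covariates are age, time since menarche, apex level, physical activity, self-efficacy and bracing compliance. All belong to the patient. The random effects and covariance structure are not described.

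**The concern.** Patients are randomised individually, but one arm is then treated in groups and the other is not. Patients who share a class and a therapist may have correlated outcomes, and this correlation would exist in the Schroth arm only (a partially nested design). The protocol gives a route for it: it says that classes raise compliance, so the group is meant to act on its members.

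With positive correlation, the mean change in the Schroth arm is less precise than 129 independent patients would make it. Two things follow. The planned power falls short of 80%. And if the model has no term for the correlation, the standard error of the treatment effect is too small and the one-sided test favours exercise more often than 5% of the time when the average effect is zero. A site term common to both arms would not deal with this, since the correlation is confined to one arm.

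The same model serves every outcome. That includes the SRS-22, which the Procedures part lists as primary beside the radiographic measures.

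**Working it through.** **Inputs from the protocol.** 129 per group, standardised effect 0.31, one-sided alpha 0.05, power 80% (section 4.2, item 5.0).

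**Inputs that are assumptions.** Class size m = 5 to 13 and ICC = 0.01 to 0.10, in the Schroth arm only.

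**Step 1: reproduce the plan's figure.** For independent patients, n per group = 2 × [(1.645 + 0.842)/0.31]² = 128.7, rounded up to 129. Power at 129 per group: noncentrality = 0.31 × √(129/2) = 2.490; the normal approximation gives 80.1% and the noncentral t (256 df) gives 79.9%. A two-sided test would need 164 per group. The stated figure is therefore the one-sided calculation for independent patients with a design effect of 1 and no slack.

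**Step 2: add correlation in one arm.**
- Design effect in the Schroth arm: DE = 1 + (m − 1) × ICC. In controls it is 1.
- Standard-error factor for the group difference: f = √[(DE + 1)/2].
- One-sided error of a test that ignores the correlation: 1 − Φ(1.645/f).
- Power of a test that respects it: noncentral t with noncentrality 2.490/f and Satterthwaite df = (DE + 1)² / [DE²/(k − 1) + 1/128], where k = 129/m.

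**Step 3: one case in full (ICC 0.05, m = 8).** DE = 1 + 7 × 0.05 = 1.35. f = √(2.35/2) = 1.084. Error = 1 − Φ(1.645/1.084) = 6.5%. k = 16.1, df = 5.5225/(1.8225/15.125 + 1/128) = 43, noncentrality = 2.490/1.084 = 2.297, power = 73%. The effect detectable with 80% power is about 0.310 × 1.084 = 0.336, so about 0.34.

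**Step 4: the range.**

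| ICC | Per class | DE | f | Error if ignored | Power if respected |
|---|---|---|---|---|---|
| 0.01 | 5 | 1.04 | 1.010 | 5.2% | 79% |
| 0.01 | 8 | 1.07 | 1.017 | 5.3% | 78% |
| 0.01 | 13 | 1.12 | 1.030 | 5.5% | 76% |
| 0.05 | 5 | 1.20 | 1.049 | 5.8% | 76% |
| 0.05 | 8 | 1.35 | 1.084 | 6.5% | 73% |
| 0.05 | 10 | 1.45 | 1.107 | 6.9% | 71% |
| 0.05 | 13 | 1.60 | 1.140 | 7.5% | 68% |
| 0.10 | 8 | 1.70 | 1.162 | 7.8% | 68% |

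**Step 5: check by simulation** (40,000 runs per case). At ICC 0.05 and 8 per class, ignoring the classes gave an error of 6.3%; respecting them gave 5.0%, with power 73.4%. At ICC 0.10 and 8 per class the figures were 7.7%, 4.9% and 68.3%. These agree with the formulas.

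**The case against.** The strongest reply is that the Analyses part does not say that patients are treated as independent. It names a mixed model, and a mixed model can carry a class or therapist effect. Random-effects detail is commonly left to the statistical analysis plan, which is not at hand. This stands. A reader might infer that the planned intervals are too narrow as a matter of fact, and the protocol does not support that. Narrow intervals follow only if the term is left out and the correlation is positive.

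The size is not documented either, and there are reasons to expect a low correlation. Home exercise takes 7 × 30 minutes = 3.5 hours a week against one hour in class, an algorithm guides each patient's prescription, and the Cobb angle is read by an evaluator blind to group. If exercise changed no patient's Cobb angle, the classes would not themselves create correlation in it; the inflated error belongs to the case of a zero average effect with real differences between classes. These points stand for the Cobb angle. They carry less weight for the self-reported SRS-22.

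A reader might also picture each therapist as one large cluster, with a far greater loss. The protocol does not say how many therapists there were or how patients were divided among them, so nothing supports a figure for that case.

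Finally, the protocol describes neither fixed class assignment nor attendance records. Patients enter at routine clinic visits, so class membership may have changed over time, and the few patients still in treatment during COVID-19 were seen individually or by video. This bears on how the remedy is built, not on whether the power figure allows for clustering.

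**Conclusion.** The point holds in a conditional form. It is certain that group delivery is confined to one arm in the primary period and that the 80% power contains no allowance for it. A later analysis plan cannot alter that second fact, because the power claim is made in the protocol itself. The protocol also specifies no term for the correlation, although it does not exclude one.

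What follows for the error rate and power depends on an ICC and a class size that have to be assumed. At ICC 0.01 and 5 to 8 per class the effect is small: error 5.2-5.3%, power 78-79%. At ICC 0.05 and 5 to 13 per class, error is 5.8-7.5% and power falls from 76% to 68%. At ICC 0.10 and 8 per class they are 7.8% and 68%. The Cobb angle probably lies nearer the low end than the SRS-22. The departure is anti-conservative and, with a one-sided test, favours exercise. A cheap correction is therefore worth making.

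**What to change.** In Analyses, specify a class-level random effect that applies to the Schroth arm only, with each control as a singleton and Satterthwaite or Kenward-Roger degrees of freedom. Define membership by the class each patient started with and record it in the existing study database. If classes were not stable, use the therapist instead. If membership rolled over time, add a sensitivity analysis by therapist or by each patient's main class. With few therapists a therapist variance may be poorly estimated, so class is the preferred level where it can be defined.

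In the sample size justification, say that the 80% assumes no clustering and give the power over a stated range of ICC and class size. For example: about 73% at 0.31, or 80% at about 0.34, for ICC 0.05 and 8 per class.

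Section 4.5 reports that enrolment is complete, and no more patients are needed. The cost is one model term, one field per Schroth patient (with some work to recover it if class membership was not recorded), slightly wider intervals and a less favourable stated power. If the estimated class variance is near zero, the result will hardly change.

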#### Procedures

At routine scoliosis clinic visits a nurse will determine eligibility and randomize participants to the observation (control) or the Schroth

exercise group. Outcomes will be measured at baseline, 3 and 6 months. Primary outcomes include baseline and 6-month radiographic curve measurements and SRS-22 questionnaire. Secondary outcomes will include postural measures (Surface Topography), Global Rating of Change (GRC), Self-efficacy questionnaire, pain, and back muscle endurance. Predictors of success will be collected at baseline.

Controls will receive the current standard of treatment for 6 months (Observation or brace prescribed as per SRS guidelines). Patients treated with Schroth exercises will participate weekly in supervised Schroth exercises and complete a daily home program for 6 months. The baseline and 6-month exam will be completed within 2 weeks of a scoliosis clinic visit with a follow-up at 3 months. After 6 months, controls will crossover to the treatment group. After 12 months and for every scoliosis visit afterwards until discharge, we will also extract the radiograph and SRS-22 questionnaire from the Edmonton Scoliosis records

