## 2.0 **\* Describe and justify the inclusion criteria for participants (e.g. age range, health status, gender, etc.):**

Patients with Adolescent Idiopathic Scoliosis (AIS), with juvenile idiopathic scoliosis (JIS), or syringomyelia without chiari from the Specialized Scoliosis Clinic in Edmonton, Calgary, Montréal (n=208) will be recruited from our scoliosis clinics. AIS is defined as idiopathic scoliosis diagnosed between the ages of 10-16. JIS is defined as idiopathic scoliosis diagnosed between the ages of 5-10. Idiopathic scoliosis may have appeared between the ages of 5-10, but not been diagnosed until after the age of 10. Therefore, including patients with JIS and AIS in the study is not including two distinct forms of scoliosis, rather a continuum of idiopathic scoliosis. Patients with syringomyelia without chiari are common and does not exclude a patient's diagnosis as AIS or JIS.

Only females are targeted. Females are more frequently severely affected to levels justifying a treatment prescription. Other inclusion criteria are:

(1) magnitude of spinal curve 10° to 45° (Cobb angle),  
 -Larger curves meet the clear indication recommended by the Scoliosis Research Society to be prescribed surgery. Small curves in skeletally immature adolescents have higher risk of progression. Curves over 30° are more likely to progress after skeletal maturity. European consensus for conservative treatment recommends exercises alone below 20° and exercises in combination with a brace for patients with curves greater than 20°.

(2) may be treated with or without brace  
 -We have broadened inclusion criteria to be inclusive of all conservative treatment offered at the Specialized scoliosis clinic in Edmonton, Calgary and Montréal (observation and bracing). European consensus for conservative treatment recommends exercises alone below 20° and exercises in combination with a brace for patients with curves greater than 20°. Including patients with and without brace treatment allows for comparison of exercise alone and in combination with brace treatment. Including brace treatment as a potential predictor of treatment success is representative of decisions clinicians are making in the treatment of patients with scoliosis. We will examine whether bracing in combination with exercises is predictive of success beyond the other treatment combinations.

(3) Risser 0-3 (indicating Incomplete skeletal maturity)  

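### Outcomes are compared on change from baseline without stated adjustment for the outcome's own baseline value, which gives up some precision and leaves chance baseline imbalance in the estimate

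*Protocol*

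**What the plan says.** The Analyses part of protocol section 2.1 states that "linear mixedmodel analyses will be used to assess differences in group changes from baseline, to 3 and 6-month while adjusting for covariates", and that "Separate analyses will be conducted for each outcome". The candidate covariates are given in a bracket: "age, time since menarche, apex levels, physical activity, self-efficacy, and bracing compliance may have associations with risk of progression". The multivariable models then take in "covariables found significant at" P=0.20 in univariate models, after a check for multicollinearity. The bracket does not list the baseline value of the outcome being analysed, and the text does not say that the groups share a common baseline mean.

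The baseline values will exist. The Procedures part says "Primary outcomes include baseline and 6-month radiographic curve measurements and SRS-22 questionnaire", and it schedules outcome measurement at baseline, 3 and 6 months.

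The sample size (section 4.2, item 5.0) is set on the same scale. It is chosen to "detect a 0.31 effect size when comparing the change in outcomes between the exercise and control groups", with 129 per group, 80% power and a one-sided alpha of 0.05.

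**The concern.** Comparing changes fixes the slope of the 6-month value on the baseline value at 1. The actual slope is usually below 1 because of measurement error and regression to the mean. Two things follow.

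- **Precision.** Part of the baseline noise is carried into the change score, so the standard error is larger than it needs to be.
- **Chance imbalance.** If the arms differ at baseline by chance, the arm that starts higher tends to fall back more. A change-score contrast counts that as treatment effect, or lets it mask one.

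The trial is planned at 80% power with a one-sided test, so it has little margin to spare. The point is separate from how the six listed covariates are screened: all six could be kept and the outcome's own baseline would still be unadjusted.

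**Working it through.** **Inputs from the protocol (section 4.2, item 5.0):** n = 129 per group, effect d = 0.31 in SDs of change, one-sided alpha 0.05, power 80%. **Assumed, because the protocol gives neither:** the baseline-to-6-month correlation rho, taken over 0.5 to 0.95, and equal SDs at the two times.

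**1. The plan's own figure.** n = 2(1.645 + 0.842)²/0.31² = 128.7, so 129 per group. By the noncentral t distribution with 256 degrees of freedom and noncentrality 0.31 × √(129/2) = 2.49, power is 79.9%. The plan's figure reproduces.

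**2. Variance ratio.** Let the outcome SD be 1 at both times.
- Variance of the change: 2(1 − rho).
- Variance of the 6-month value given baseline: 1 − rho².
- Ratio, adjusted to change: (1 − rho²)/[2(1 − rho)] = (1 + rho)/2.

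Adjustment therefore acts as if the effect were 0.31/√((1 + rho)/2) at the same n.

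**3. Power at 129 per group after adjustment.**

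| Assumed rho | Variance ratio | Equivalent effect | Power |
|---|---|---|---|
| Change score, as planned | 1 | 0.310 | 79.9% |
| 0.5 | 0.75 | 0.358 | 88.9% |
| 0.7 | 0.85 | 0.336 | 85.3% |
| 0.8 | 0.90 | 0.327 | 83.5% |
| 0.9 | 0.95 | 0.318 | 81.7% |
| 0.95 | 0.975 | 0.314 | 80.8% |

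At rho 0.5 the gain equals having 129/0.75 = 172 per group analysed by change score. Simulation at 129 per group gave variance ratios of 0.78, 0.91 and 0.97 at rho 0.5, 0.8 and 0.95, against 0.75, 0.90 and 0.975 by formula.

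**4. Chance imbalance.** A baseline difference of one standard error is √(2/129) = 0.1245 outcome SDs. It moves the change-score estimate by (1 − rho) × 0.1245 outcome SDs. Dividing by the SD of change, √(2(1 − rho)), gives 0.1245 × √((1 − rho)/2):
- rho 0.5: 0.062, or 20% of the 0.31 target
- rho 0.8: 0.039, or 13%
- rho 0.95: 0.020, or 6%

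**5. Does a mixed model recover this by itself?** On one simulated data set (rho 0.6), a mixed model with baseline in the response, separate group means at baseline and a group-by-time contrast gave SE 0.110. That is the same estimate and SE as the plain change-score comparison. Adjusting for baseline gave SE 0.096, and constraining the groups to a common baseline mean gave 0.097. The saving depends on the adjustment or the constraint.

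**6. Unequal SDs.** With k = SD at 6 months / SD at baseline, the slope is rho × k and the variance ratio is k²(1 − rho²)/(1 + k² − 2 rho k). As an illustration only, rho 0.9 and k 1.1 give a slope of 0.99 and a ratio of 0.2299/0.2300, so nothing is gained. The factors in steps 2 and 4 apply only when k = 1.

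**The case against.** **The wording does not exclude baseline adjustment.** The protocol does not say that the dependent variable is a change score. A longitudinal model with a common baseline mean would also assess differences in change, and the covariate sentence speaks of all relevant covariates. Such detail may also be settled in a statistical analysis plan that is not shown. This stands in part: the text leaves room for the better model. But the protocol itself fixes the contrast, the candidate list and the selection rule, and none of these secures the adjustment. A baseline value added to the list would still have to pass the P=0.20 screen, so it could be in the model for one outcome and out for another.

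**Not every outcome is affected.** The Global Rating of Change is itself a rating of change and has no baseline value. Self-efficacy is both a secondary outcome and a listed covariate, so its own baseline may already be a candidate. Both exceptions stand.

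**The gain may be small where it matters most.** The Objectives make Cobb angle the main outcome and put quality of life among the secondary ones, although Procedures lists SRS-22 with the primary outcomes. If rho for Cobb angle is 0.8 to 0.95, the gain is about 1 to 4 points. That stands.

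**Carried-forward values shrink it.** With last value carried forward, a patient with no follow-up has a final value equal to baseline. If 20% were in that position, an upper bound given the expected completion above 80%, rho 0.5 would become 0.8 × 0.5 + 0.2 = 0.6. By step 3, power would then be 87.1% rather than 88.9%. This stands as a qualification.

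**Two stronger readings are tempting.** A reader might infer that the planned analysis is biased, or that the sample size is wrong. The documents support neither. Under randomisation the change contrast is unbiased on average, and the imbalance effect is conditional on a baseline difference that is not known to exist. The 129 per group reproduces for the contrast it was calculated for.

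**Conclusion.** The point holds as a matter of efficiency and of protection against chance imbalance, not of validity. For outcomes measured at baseline, the protocol commits to a contrast that is less precise than one it could have from data already being collected, and it names no adjustment that would correct this.

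The size depends on a correlation that the protocol does not give. With equal SDs, the power gain at 129 per group runs from about 9 points at rho 0.5 to about 1 point at rho 0.95. It is probably at the low end for Cobb angle and may be larger for SRS-22, pain and endurance; these placings are judgements, not figures from the protocol. Unequal SDs or carried-forward baseline values would change the numbers, and a slope close to 1 would remove the gain. The change is worth making because it costs almost nothing.

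**What to change.** In the Analyses part of section 2.1, state that for each outcome with a baseline measurement the follow-up values (3 and 6 months, or 6 months only where there is no 3-month measurement) are modelled with that outcome's own baseline value as a pre-specified fixed covariate, outside the P=0.20 screen. Alternatively, keep baseline in the response and constrain the groups to a common baseline mean. Report the adjusted group difference at 6 months. Adding baseline to the candidate list alone is not enough, because the screen would then decide whether it stays. The Global Rating of Change needs no such term.

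The sample size can stay as stated; it becomes slightly conservative. The cost is one degree of freedom per model and a protocol amendment, with no new data, visits or patients. Section 4.5 says that enrolment is complete, and the analysis is to pool 50 pilot patients (50/258, about 19% of the total) for whom a Cobb effect size is already known. The amendment should therefore be dated before the main trial data are analysed.
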